### Recruitment {15}

Participants are recruited from two day clinic groups, which collectively treat 56 patients at any given time, each undergoing a 12-week treatment program. This corresponds to an average screening rate of five patients per week. Assuming the majority of patients meet the eligibility criteria, an average enrollment rate of 1.5 participants per week is anticipated, resulting in a projected recruitment period of 1.5 years. If necessary, the recruitment period may be extended to a maximum of 2 years.

### Assignment of interventions: allocation

#### Sequence generation {16a}

Participants are randomly allocated in a 1:1:1 ratio to one of two PA coaching conditions (with or without continuous support after post-intervention) or to a control condition receiving general information about health-enhancing PA. The allocation sequence was computer-generated using the Sealed Envelope^™^ randomization service (Sealed Envelope Ltd., London, UK), employing random permuted blocks of 3 and 6. Randomization is stratified by age (< 35 years vs. ≥ 35 years) and sex (male vs. female) to ensure balanced distribution of these variables across the three study arms. The randomization list was prepared by an independent researcher not otherwise involved in participant recruitment, enrollment, or assessment.

#### Concealment mechanism {16b}

After the randomization list was generated, a staff member employed at DSBG who has no further role in the study except data monitoring used it to prepare sealed envelopes with treatment assignments, ensuring allocation concealment.

#### Implementation {16c}

After completing the baseline assessment, each participant draws a sealed envelope to determine their allocation. The research assistant who conducts the assessments then informs the participants of their assigned condition.

### Assignment of interventions: blinding

#### Who will be blinded {17a}

Because of the behavioral nature of the intervention, participants and researchers cannot be blinded.

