**Fig. 1 Fig1:**
[figure not shown]
Overview of the study design

Participants (*N* = 114) are randomized (stratified by sex and age) to one of two PA coaching conditions (with or without continuous support after post-intervention) or to a control condition (written information on health-enhancing PA) [81]. Given the behavioral nature of the intervention, neither participants nor researchers are blinded. To reduce assessment bias, the primary outcome (PA behavior) is assessed device-based using a thigh-worn accelerometer device.

The trial features several pragmatic elements [82–84], such as integration into treatment as usual, delivery in real-world and authentic settings (e.g., home-based components), and use of a commercially available smart ring for self-monitoring. Coaching protocols are adapted for clinical populations, and outcomes focus on clinically relevant indicators, including depressive symptom severity and quality of life.

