### Secondary outcomes

#### Self-reported physical activity

The 7-Day Physical Activity Recall (7DPAR) is used to assess participants’ self-reported PA through a structured 20-min interview by a trained research assistant [110–112]. The 7DPAR assesses all PA bouts of at least 10-min duration over the past 7 days. For a PA bout to be recorded, intensity needs to be at least moderate [112]. Interviewers record breaks during PA, which are subtracted from total durations. In addition to total minutes of PA in moderate, moderate to vigorous, and vigorous intensity per week, the 7DPAR also captures strength and flexibility training. As part of this study, the 7DPAR is supplemented by a question on participation in structured exercise and sports programs. This latter component is particularly relevant, as the coaching intervention aims to support engagement in such programs [113].

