#### Depressive symptom severity

Depression severity is assessed using the Hamilton Depression Rating Scale (HAMD-17) [114] and the self-report Beck Depression Inventory-II (BDI-II) [115, 116]. The HAMD-17 is administered as a structured clinical interview by trained study personnel. The BDI-II is a 21-item questionnaire that assesses affective, behavioral, cognitive, and somatic symptoms of unipolar depression. Total scores range from 0 to 52 for the HAMD-17 and from 0 to 63 for the BDI-II, with higher scores indicating greater depression severity. Both instruments demonstrate acceptable reliability and validity [117–119]. Treatment response is defined as a ≥ 50% reduction in HAMD-17 score from baseline to endpoint, partial response as a 25%–49% reduction, and nonresponse as a < 25% reduction. Remission is defined as a HAMD score ≤ 7 [120]. For the BDI-II, response is similarly defined as a ≥ 50% reduction and remission as a score ≤ 9; no consensus definitions exist for partial response [121]. According to the German S3 clinical guidelines [122], HAMD-17 scores ≥ 17 indicate at least moderate depression, whereas a BDI-II score of ≥ 20 reflects moderate symptom severity [123, 124].

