## Oversight and monitoring

### Composition of the coordinating center and trial steering committee {5d}

PACOUTPAT is conducted as a single-center trial at the Sonnenhalde AG Psychiatric Clinic. The study is implemented by the Department of Sport, Exercise and Health (DSBG) of the University of Basel at the Sonnenhalde AG site.

The sponsor-investigator (MG) from the University of Basel is responsible for the overall coordination and quality assurance of the trial, including implementation in accordance with the protocol, data management and analysis, staff instruction, and dissemination of findings. Day-to-day trial operations are led by an affiliated doctoral student (CS) who oversees participant recruitment, data assessments, and intervention delivery. The doctoral student is supported by a research assistant who assists with recruitment, data collection, and communication with patients. PA coaches, all with a background in sport and exercise science, are trained by the doctoral student and deliver the intervention according to standardized procedures. The co-principal investigator ([name], chief physician of Sonnenhalde AG) is responsible for the implementation of clinical treatment and the supervision of patients. Furthermore, he ensures favorable recruitment conditions by integrating the intervention into treatment as usual and establishing effective communication between clinic staff and DSBG personnel. Clinic staff support recruitment by informing eligible patients about the study and encouraging contact with the research team.

The study team maintains structured communication through the following:Weekly to monthly meetings between the sponsor-investigator and the doctoral studentWeekly to biweekly meetings between the doctoral student and the research assistantWeekly to monthly meetings between the doctoral student or research assistant and the PA coachesWeekly meetings between the doctoral student or research assistant and the clinic staff

Additionally, an annual team meeting is held with the broader research team, including the sponsor-investigator, co-principal investigator, doctoral student, research assistant, PA coaches, and co-authors, to review study progress and coordinate next steps.

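### The reason given for having no blinding does not cover the HAMD-17 interviewer, and an assessor announces the arm, so this rated secondary outcome can be biased

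*Protocol article*

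**What the plan says.** The blinding section ({17a}) reads: "Because of the behavioral nature of the intervention, participants and researchers cannot be blinded". It makes no exception for outcome assessors, and the trial design section says the same.

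Under Implementation ({16c}), the envelope is drawn after the baseline assessment, and then: "The research assistant who conducts the assessments then informs the participants of their assigned condition".

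Two secondary outcomes are collected by interview:
- HAMD-17: "The HAMD-17 is administered as a structured clinical interview by trained study personnel".
- 7DPAR: a "structured 20-min interview by a trained research assistant", in which "Interviewers record breaks during PA, which are subtracted from total durations".

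One protection against assessment bias is named, in the text under Fig. 1: "To reduce assessment bias, the primary outcome (PA behavior) is assessed device-based using a thigh-worn accelerometer device".

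On staffing, the section on the coordinating center ({5d}) gives the coaching to PA coaches and day-to-day operations to a doctoral student. It adds: "The doctoral student is supported by a research assistant who assists with recruitment, data collection, and communication with patients". Meetings with the coaches may be held by either the doctoral student or the research assistant.

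**The concern.** A behavioural intervention cannot be hidden from those who receive or deliver it. Whether an outcome interviewer can be kept unaware is a separate question, and the article answers it with the same sentence. The disclosure step then works against masking: the arm is announced by someone who conducts assessments, although nothing in the intervention requires that.

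The stake is the secondary objective on depression severity. The HAMD-17 depends on the rater's judgement of what the patient says. A rater who knows the arm, and belongs to the team testing the coaching, may score coached patients somewhat lower without meaning to. The article's other depression measure, the BDI-II, is self-reported by participants who know their arm. No depression measure is therefore collected masked.

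**Working it through.** No arithmetic is needed to establish the point. It follows from setting the sections side by side.

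1. **Does the stated reason reach the interviewer?** Section {17a} rests on the behavioural nature of the intervention. Section {5d} gives delivery to the PA coaches and describes the research assistant's work as recruitment, data collection and patient communication. The reason covers the coaches and participants but not that assistant.
2. **When does the assessor learn the arm?** Under {16c} this happens after baseline. The T0 ratings are made before allocation, so the exposure is at T1 and T2, which are the two outcome times in the mixed model.
3. **Which outcomes are exposed?** The HAMD-17 is interviewer-rated and is named in {20a} as a mixed-model outcome. The 7DPAR has some interviewer input (breaks are recorded and subtracted) but is not in that list. The accelerometer outcome does not pass through a rater.
4. **Does the point touch the plan's own figures?** No. The sample size concerns the primary outcome and is reproduced by the repeated-measures interaction form with 3 groups and 3 times. λ = f²·N·m/(1−r) = 0.175² × 87 × 3 / 0.5 = 15.99, with 4 and 168 degrees of freedom, gives power 0.903. Then 87 × 1.3 = 113.1, rounded up to 114. Masking a rater leaves this unchanged.

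**Illustration of size.** The documents give neither a HAMD-17 SD nor a rater shift. Assumed: SD 6, a shift b of 1 or 2 points towards coaching, no true effect, normal approximation, one coaching arm against control at one time point.

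*Simple comparison, everyone retained* (114/3 = 38 per arm, two-sided 5%, critical value 1.96):
- SE = 6 × √(2/38) = 1.376.
- b = 1: 1/1.376 = 0.727. P(Z > 1.233) + P(Z < −2.687) = 0.112.
- b = 2: 2/1.376 = 1.453. P(Z > 0.507) + P(Z < −3.413) = 0.306.
- With no shift the rate is 5%.

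*Closer to the plan* (30% loss: 38 × 0.7 = 26.6, taken as 27 per arm; baseline correlation assumed 0.5; Dunnett critical value about 2.21 for two comparisons with one control):
- SE = 6 × √(1 − 0.5²) × √(2/27) = 1.414.
- b = 1: 1/1.414 = 0.707. P(Z > 1.503) + P(Z < −2.917) = 0.068.
- b = 2: 2/1.414 = 1.414. P(Z > 0.796) + P(Z < −3.624) = 0.213.
- With no shift the rate for this single comparison is 2 × P(Z > 2.21) = 0.027, so 7% and 21% are to be read against 2.7%, not 5%.

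Both versions ignore the concurrent physical-activity term that {20a} adds to the secondary-outcome models.

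**The case against.** The strongest reply is that the trial is openly declared open-label, its primary outcome is protected by a device, and the HAMD-17 is a structured interview by trained staff under standard operating procedures. All of this is true and keeps the point off the primary result. None of it masks the rater, and declaring a trial open-label does not support the word cannot where assessors are concerned.

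The second reply is that masking would be leaky. Coached participants wear a ring until follow-up. The 7DPAR asks about structured programmes, which the coaching promotes. The satisfaction questionnaire goes only to coached arms, and assessment reminders reach the arms by different routes. The HAMD-17 also draws on what unmasked patients report. This stands: the remedy would be partial and would remove only the rater's share of the bias.

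The third reply is timing. Recruitment began in June 2025, so some participants had their arm announced by the assessor. This also stands, and affects how the change is made.

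Several stronger readings are tempting but not supported:
- A reader might infer that the HAMD-17 *is* biased. The documents show a risk, with no direction or size. The probable direction is a judgement.
- A reader might infer that the assistant who announces the arm is the HAMD-17 rater. The article says only that trained study personnel administer it. The point survives because {17a} leaves all researchers unblinded.
- A reader might infer that the 7DPAR interviewer decides whether a bout reaches moderate intensity. Who classifies intensity is not stated; only the recording of breaks is.
- A reader might infer that response and remission rates are distorted. They are defined from the HAMD-17, but {20a} plans no analysis of them.

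**Conclusion.** The point holds as a correctable weakness in the handling of a secondary outcome. The reason in {17a} does not extend to an interviewer who delivers no coaching, and {16c} unmasks an assessor without need. The HAMD-17 results at T1 and T2 can therefore be biased, probably in favour of coaching. The 7DPAR is exposed to a lesser degree.

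The size cannot be derived from the documents. The false-positive rates of about 11% and 31%, or about 7% and 21% under assumptions nearer the plan, show what shifts of 1 and 2 points would do. They depend on the assumed SD, shifts and correlation; the conclusion does not. That the present team could mask the interviewer is an inference from the roles in {5d}. It is less certain than the point itself.

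**What to change.** Amend {16c} and {17a} along these lines:

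- The envelope is opened with, and the arm announced by, the doctoral student or a coach, never the person who interviews at T1 or T2.
- The T1/T2 HAMD-17 and 7DPAR interviewer is named by role, has no access to allocation or coaching records, and does not attend coach meetings. The doctoral student takes those meetings, which {5d} already allows.
- Arm-specific communication, such as control-group assessment notices and the booklet, is sent by someone else.
- The HAMD-17 comes first at each visit, before the 7DPAR question on structured programmes, the satisfaction questionnaire and any feedback.
- Participants are asked not to disclose their arm and to keep the ring out of view during the interview.
- The rater records a guess of the arm after the HAMD-17, so that the success of masking can be reported.
- {17a} states who is masked, who is not, and that masking is partial.

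Cost: the sample size and visit schedule are unchanged. Tasks move among roles already described, though a coach attending every draw, controls included, may not be free of cost, so the doctoral student is the easier choice. Ethics approval is needed before the change. Ratings already made unmasked, and later ratings of participants whose arm the interviewer already knows, should be flagged so that they can be examined separately. Reporting bias from unmasked participants remains. If the change proves unworkable, {17a} should at least replace the claim that blinding is impossible with a plain statement that assessors are not masked and that the HAMD-17 carries that risk.

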#### Procedure for unblinding if needed {17b}

This is not applicable, as the study is open-label.

## Data collection and management

### Plans for assessment and collection of outcomes {18a}

All outcome measures are systematically recorded on-site at the day clinic across the three measurement timepoints. To ensure methodological consistency and data integrity, all study personnel have undergone rigorous training and adhere to standardized operating procedures. Participant responses to the questionnaires are captured electronically via REDCap to minimize transcription errors and enhance data accuracy. The rationale underpinning the selection of specific measurements, as well as their reliability and validity, is described under the " Outcomes {12}" section.

### Plans to promote participant retention and complete follow-up {18b}

In week 26 of the 36-week study period, corresponding to 16 weeks post-completion of the day clinic treatment, participants in all three groups receive a small token of appreciation by mail from the study team. The token consists of a thank-you postcard, a small motivational sticker, and a piece of chocolate. All items are non-monetary and of minimal value and are intended to acknowledge participants’ contributions to the study and to promote sustained engagement in the completion of follow-up study procedures.

For participants allocated to the intervention groups, upcoming data assessments are integrated into ongoing coaching sessions as part of the established protocol. In contrast, participants in the control group are notified of forthcoming assessments via written communication.

Importantly, individuals who discontinue participation in the intervention are still invited to complete scheduled data assessments, thereby supporting the integrity and completeness of longitudinal data collection.

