### Intervention description {11a}

Participants in both intervention groups continue to receive treatment as usual according to the Swiss treatment guidelines for MDD [86]. The intervention is designed to provide individually tailored support and encouragement to increase PA during and after clinical outpatient treatment for a period of up to 36 weeks (= 10 + 26 weeks).

### Intervention Group 1

Participants in IG1 receive a 10-week PA coaching program guided by a trained personal PA coach. The coaching follows an interest- and experience-based approach aimed at identifying PA opportunities that align with participants’ individual preferences and promote positive affective experiences. Where appropriate, structured PA is preferred over unstructured forms to leverage the benefits of group-based and/or supervised exercise, such as increased social support and accountability. The coaching approach is individualized and flexible, supporting unstructured PA when it better matches the participant’s interests and enjoyment. The primary focus is on promoting pleasure and well-being during PA with the ultimate goal of facilitating long-term adherence.

The coaching begins with a 60-min introductory session during which the coach and participant get to know each other, review the structure and goals of the program, and assess the participants’ current life situation and PA status using a standardized questionnaire [87]. Participants’ previous PA experiences and preferences are also explored. To identify individual motives and goals related to PA, the Bernese Motive and Goal Inventory [88] is administered.

In the second session, these motives and goals are reviewed and reflected upon to derive personal implications for PA engagement. A first structured PA session is identified, and relevant logistical and motivational conditions for attendance are established. The third session involves attending this first exercise session together with the coach providing on-site support. During this and subsequent sessions, affective responses are monitored using the Feeling Scale [89], the Felt Arousal Scale [90] is used to assess perceived activation, and the Borg Perceived Exertion Scale [91] is administered for the definition of exertion.

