Sessions 4 to 9 alternate between attending structured PA sessions and reflective sessions. These reflective coaching sessions involve evaluation of experiences, discussing whether specific activities should be continued or adapted, and planning future participation to optimize enjoyment and fit with individual preferences.

All 10 coaching sessions are conducted face-to-face in the participant’s personal environment to maximize individual support and real-world applicability. Each session is scheduled to last approximately 60 min.

To further facilitate behavior change, the coaching is supported by a wearable smart ring, adhering to 12-point WATCH (Wearable Activity Tracker Checklist for Healthcare) guidelines [92]. Specifically, the Oura Ring (Generation 3; Ōura Health Oy, Finland) is used. The lightweight device (4–6 g) includes a 50-Hz triaxial accelerometer, NTC thermistor, and photoplethysmograph to continuously measure movement, body temperature, heart rate, heart rate variability, and respiration [93]. The ring is worn on the nondominant hand (index, middle, or ring finger). The device comes with a 6–7-day battery life and uploads data to both a smartphone app and a secure cloud dashboard. This allows coaches to monitor participants’ PA levels, energy expenditure, and sleep patterns. Participants in IG1 continue to wear the ring after the end of the 10-week coaching program until follow-up.

### Intervention Group 2

Participants assigned to IG2 receive the same 10-week interest- and experience-based coaching as IG1 and also continue to wear the Oura Ring until follow-up. However, unlike IG1, IG2 remains in contact with the coach for an additional 6 months (26 weeks) to receive cognition-based coaching aimed at promoting sustainable behavior change.

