During this phase, biweekly phone calls are conducted to assess participants’ PA habits and adherence to their routines, offering support if difficulties arise. These brief (~20-min) phone sessions focus on applying evidence-based behavior change techniques (BCTs) to reinforce long-term habit formation [94]. Strategies include structured activity planning, identifying and overcoming barriers, leveraging social support, and relapse management. The goal is to enhance self-regulation and resilience, ensuring that participants maintain their achieved activity levels beyond the initial intervention period. A detailed description of the intervention procedures is provided in the Intervention Guide, which is available as Additional file 1.

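### The stated route for announcing assessments is not available to IG1 at T2, so prompting to return for the primary outcome differs by arm at week 36

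*Protocol article*

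**What the plan says.** The section on participant retention {18b} describes a single route for both intervention groups, without telling them apart: "upcoming data assessments are integrated into ongoing coaching sessions as part of the established protocol". It then sets out a different route for the third arm, where "participants in the control group are notified of forthcoming assessments via written communication".

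The intervention description {11a} limits IG1 coaching in time: "Participants in IG1 receive a 10-week PA coaching program guided by a trained personal PA coach". After that only IG2 keeps a coach: "unlike IG1, IG2 remains in contact with the coach for an additional 6 months (26 weeks" of phone support, during which "biweekly phone calls are conducted to assess participants’ PA habits and adherence to their routines". IG1 has one continuing element: "Participants in IG1 continue to wear the ring after the end of the 10-week coaching program until follow-up".

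Trial design {8} puts T1 at week 10 and T2 at week 36, with all assessments on site at the day clinics. Section {18b} also describes a small thank-you mailing to all three arms in week 26, and says that people who stop the intervention are still asked to attend assessments.

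**The concern.** The retention section treats IG1 and IG2 as one group, but from week 10 onwards they are not alike in contact. A route that depends on coaching still being under way cannot reach IG1 at T2. This is a stated procedure that conflicts with the schedule, not just a detail left out.

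What is at stake is the primary outcome at T2. Participants must come back to the clinic to be fitted with the accelerometer, long after their treatment there has ended. If the effort to bring them back depends on allocation, the share with missing data may depend on it too. That affects the planned comparisons of each intervention group with control ({20a}) and the comparison of IG1 with IG2, which section {6b} presents as the evidence on coaching duration. Section {14} already allows for 30% loss of primary outcome data, so there is room for the arms to differ.

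**Working it through.** **1. Stated prompting by arm and visit**, from {8}, {11a} and {18b}:

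| Arm | T1, week 10 | T2, week 36 |
|---|---|---|
| IG1 | coaching sessions (available) | coaching sessions (ended at week 10) |
| IG2 | coaching sessions (available) | biweekly coach calls (available) |
| CG | written notice | written notice |

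The gap for IG1 is 36 − 10 = 26 weeks. Over the same period IG2 has about 26 / 2 = 13 calls.

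**2. Does anything else stated carry the T2 notice to IG1?**

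- The week-26 mailing reaches IG1, but it comes 36 − 26 = 10 weeks before T2 and is described as a token of thanks meant to sustain engagement, not as notice of an appointment.
- The continued invitation in {18b} concerns people who stop the intervention. It does not say how they are invited, and it does not address IG1 participants who complete their coaching.
- The ring is described as self-monitoring, not as a reminder.
- Routine clinic contact has ended. Treatment lasts 12 weeks ({13}, {15}) and baseline falls 2 to 4 weeks after it starts (Abstract), so treatment ends about 8 to 10 weeks after baseline, some 26 to 28 weeks before T2.

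**3. Is this a matter of numbers or of bias?** The plan's target follows from 87 × 1.30 = 113.1, taken up to 114, or 38 per arm. At an equal 30% loss each arm keeps 38 × 0.70 = 26.6, in total 79.8. With assumed losses of 30%, 40% and 20% in CG, IG1 and IG2, the arms keep 26.6, 22.8 and 30.4, again 79.8 in total. In this illustration the total is unchanged and only the balance between arms moves. The concern is bias.

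**4. Size of a possible bias (assumed inputs only).** Let p be the share missing in an arm and g the amount by which returners exceed non-returners in activity, in SD units. The mean among returners exceeds the true arm mean by p × g, so the contrast of arm A with arm B is shifted by (p_A − p_B) × g.

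- Loss differing by 10 points, g = 0.2 to 0.5: 0.10 × 0.2 = 0.02 to 0.10 × 0.5 = 0.05 SD.
- Loss differing by 20 points, same g: 0.20 × 0.2 = 0.04 to 0.20 × 0.5 = 0.10 SD.

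On direction: if IG1 lost more than the other arms and non-returners were less active, IG1 would look too good against both CG and IG2. If IG2 lost least, IG2 would look too poor against both.

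Neither p by arm nor g is in the document. The formula is for a difference of observed means. Under the planned model, which adjusts for baseline and uses T1 and T2, plus imputation, it applies only if g is what remains after conditioning on the observed data.

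**The case against.** The best case against the point has four parts.

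*This is a condensed article.* A full protocol and standard operating procedures exist, and appointment notices are the kind of detail left to them. That would answer mere silence. Here, however, the article does state a route for the intervention groups, and that route does not fit the IG1 schedule. IG1 could be told about T2 at the last session, but that would be 26 weeks ahead and is not what the article says.

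*Mitigations are stated.* The week-26 mailing, the continued invitations, and the intention-to-treat analysis with imputation and sensitivity analyses ({20c}) all lower the risk. This stands, in part. None of them is a T2 notice to IG1. Imputation under MCAR or MAR does not remove bias if non-returners are less active than their observed data predict. Sensitivity analyses can probe that bias but not prevent it.

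*Missingness that depends on allocation is not itself a bias.* Correct. Group is in the model, so dependence on arm alone is compatible with MAR. Harm needs the further assumption in step 4.

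*IG2 may be retained better simply because it has calls for 26 weeks.* This also stands. Those calls are part of the treatment, and an identical notice would not remove their effect on retention.

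A reader might go further and infer that the procedure drives differential attrition, that the route fails for IG1 throughout, or that controls are contacted in writing and in no other way. The document supports none of these. It gives one overall attrition figure, the route works for IG1 at T1, and it does not say that writing is the only channel for controls.

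**Conclusion.** The point holds as an internal conflict with a limited consequence. Section {18b} relies on coaching sessions that, under {11a}, IG1 no longer has in the 26 weeks before T2, and the stated prompting for the primary outcome at T2 therefore differs across all three arms. At T1 the route is workable in both intervention arms, though it still differs from that in controls.

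The result is a risk of arm-dependent missing data at T2, partly offset by the measures already in the plan. The 0.02 to 0.10 SD in the working is only an illustration of residual bias from data missing not at random. It is not an estimate for this trial, and it cannot be ascribed to the mode of notice alone, because coaching contact itself may affect retention. The inconsistency is certain and its effect unknown. It is worth correcting because correction is cheap.

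**What to change.** Reconcile {18b} with the IG1 schedule. Send the same written or telephone notice of T1 and T2 from the study office to all three arms, at the same interval before each visit. Coaches may add a reminder but should not replace the notice. Report attrition and missing primary outcome data by arm at T1 and T2.

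The cost is about one extra letter or call per intervention participant per assessment. Intervention, sample size and analysis model stay as they are. The trial is under way, so the change has to be handled under the amendment section {25}. It should start in all arms on the same date, with that date recorded. With data collection planned to run to September 2027, the remaining T2 visits would benefit. The change will not remove a retention difference that arises from IG2's coaching contact itself, which is why reporting by arm is needed as well.
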